#### Sample size calculations

We plan to test the hypothesis that there are equivalent mean changes in outcome variables in intervention and control groups. We estimated that a sample size of 240 households (120 intervention and 120 control) was needed to observe significance of a medium effect size (0.5 standard deviation), in clusters of 20 households within 12 CSA program communities (intra-class correlation of 0.05; 25% attrition from pre- to post-season, 95% confidence level, and power of 0.8). This strategy should allow us to detect as significant a difference between changes in fruit and vegetable intake of approximately one-third of a serving per day.

#### Randomization

Following enrollment and baseline assessment, participants will be 1:1 randomly assigned to intervention and control groups within CSA program communities by trained research staff using a computer-generated randomizer to assure equivalent group sizes at each farm location. Randomization will take place after informed consent is obtained at study enrollment appointments. Given the nature of the intervention, neither the participants nor the study staff will be blinded to group assignment.

#### Intervention components

##### CO-CSA

The shares offered through the CO-CSA program will be identical to standard summer CSA shares offered to full-paying CSA members. If the farm offers more than one size share (e.g. small share, standard share, large share), study participants will select their preferred option. Shares can be paid for at the start of the season or on a weekly basis at pick-up using cash, EBT, and another form of payment accepted by the farm. Participants will be sent reminder messages for the first 4 weeks of the CSA season.

##### Curriculum

Educators will deliver the curriculum developed in component 3 on consecutive weeks in three-lesson clusters during early, mid-, and late CSA season, with timing determined by performance centers based on the local harvest calendar. The classes will be scheduled for days, times, and locations that are convenient for most participants. Participants will be encouraged to attend all classes and will be reminded of the date and time of each session by the local educator. Handouts will be provided so that participants can share what they learn with non-attending family members and a password-protected project website will be developed where participants who are unable to attend classes will be able to access materials that align with lesson content, including lesson handouts and recipes that feature common CSA vegetables.

##### Kitchen tools

To help participating families prepare their CSA produce, free kitchen tools will be provided. Participants will be able to select two to four of the following items: food processor, crockpot, stockpot, large cutting board, chef’s knife, salad spinner, reusable grocery bag. Participants will choose kitchen tools just prior to their first year of CO-CSA participation. These kitchen tools will be mailed directly to participants’ homes. Additionally, a vegetable peeler, vegetable scrub brush, and paring knife will be distributed at the healthy eating classes for participants to keep.

##### Data collection and outcomes

We will assess changes from baseline in the quantity and variety of fruits and vegetables consumed, intake of energy-dense and processed foods, and dermal carotenoid levels for both children and adults. We also will measure estimated energy intake and dietary quality for children, food-related changes in the household environment (including household food security), caregivers’ knowledge and skills related to healthy eating, and children’s BMI percentile, physical activity, and sedentary behavior (Table 4).

**Table 4 Tab4:** Primary and secondary outcome measures for component 4 (randomized trial)

Outcome	Measure	Source/Instrument
Primary outcomes		
Child’s fruit and vegetable intake	• Fruit and vegetable screener	• National Cancer Institute’s All-Day Fruit and Vegetable Screener [82]^a^
	• Three dietary recalls	• Automated Self-Administered 24-h dietary recall (ASA24–2016™) [73]
Child’s intake of sugar-sweetened beverages and processed snacks	• Beverage and snacks questionnaire	• Beverage and snack questionnaire 2 (BSQ2) [84, 85]^a^
	• Three dietary recalls	• Automated Self-Administered 24-h dietary recall (ASA24–2016™) [73]
Child’s caloric intake as a percent of estimated energy requirements	• Three dietary recalls	• Automated Self-Administered 24-h dietary recall (ASA24–2016™) [73]
Child’s dermal carotenoid levels	• Resonance Raman spectroscopy (RRS) of the palm	• Pharmanex Biophotonic Scanner S3 (NuSkin, Provo, UT)
Child’s diet quality	• Three dietary recalls	• Automated Self-Administered 24-h dietary recall (ASA24–2016™) [73]
	• Fruit and vegetable screener	• National Cancer Institute’s All-Day Fruit and Vegetable Screener [82]^a^
	• Beverage and snacks questionnaire	• Beverage and snack questionnaire 2 (BSQ2) [84, 85]^a^
Secondary outcomes		
Child’s BMI percentile	• Height and weight measured by trained research staff	• Lohman [81]
Child’s physical activity	• Questionnaire questions	• Burdette et al. [93] and Youth Risk Behavior Survey [92]^a^
Child’s sedentary behavior	• Questionnaire questions	• Youth Risk Behavior Surveillance System (YRBSS) questionnaire [92]^a^
Caregiver’s knowledge, attitudes, and beliefs about fruits and vegetables	• Questionnaire module	• Negative Cooking Attitude scale [86]^a^, Self-Efficacy for Eating/Cooking Fruits and Vegetables scale [86]^a^, General Nutrition Knowledge Belief score [87]^a^, and original
Caregiver’s ability to select, store, and prepare CSA produce	• Questionnaire module	• Cooking Techniques and Meal Preparation Self-Efficacy Scale [86]^a^
Caregiver’s ability to substitute fruit and vegetables for energy-dense foods	• Questionnaire module	• Original
Caregiver’s ability to prepare foods to minimize added (solid) fat and sugar	• Questionnaire module	• Original
Availability and accessibility of fruits and vegetables in the home	• Questionnaire module	• Scales for fruit and vegetable availability and accessibility within the home [88]
Caregiver’s fruit and vegetable intake	• Fruit and vegetable screener	• National Cancer Institute’s All-Day Fruit and Vegetable Screener [82]^a^
Caregiver’s intake of sugar-sweetened beverages and processed snacks	• Beverage and snacks questionnaire	• Beverage and snack questionnaire 2 (BSQ2) [84, 85]^a^
Caregiver’s dermal carotenoid levels	• Resonance Raman Spectroscopy (RRS) of the palm	• Pharmanex Biophotonic Scanner S3 (NuSkin, Provo, UT)
Household food security	• Questionnaire module	• US Department of Agriculture 6-item Food Security Module with 30-day reference period [89]^a^

^a^Indicates the tool was modified or adapted

The study team at Cornell will oversee all online questionnaire-based data collection, including dietary recalls. Study staff at each performance center will travel to the community sites to collect anthropometric and dermal measures. The schedule for data collection is shown in Table 5. Data collection instruments can be requested from the Principal Investigator ([name]).

**Table 5 Tab5:** Data collection schedule: component 4 (randomized trial)

Assessments	Baseline	Fall	Spring
Informed consent form	**X**		
Physical measurements			
Anthropometric measures (child)	**X**	**X**	
Dermal carotenoid measures (caregiver and child)	**X**	**X**	
Dietary recalls (child)	**X**	**X**	
Online questionnaire modules			
Brief dietary measures (caregiver and child)	**X**	**X**	**X**
Fruit and vegetable knowledge attitudes, and beliefs (caregiver)	**X**	**X**	
Ability to select, store, and prepare CSA produce (caregiver)	**X**	**X**	
Ability to substitute fruit and vegetables for energy-dense foods (caregiver)	**X**	**X**	
Ability to prepare foods to minimize added (solid) fat and sugar (caregiver)	**X**	**X**	
Fruit and vegetable availability and accessibility within the home (household)	**X**	**X**	
Food security (household)	**X**	**X**	**X**
Nutrition assistance and education participation (household)	**X**	**X**	**X**
Physical activity and sedentary behavior measures (child)	**X**	**X**	**X**
General health status (caregiver and child)	**X**	**X**	**X**
Costs associated with food purchasing and preparation (household)	**X**	**X**	**X**
Costs associated with CO-CSA participation (household)		**X** ^**a**^	
Kitchen inventory (household)	**X**		
Household composition and demographics	**X**	**X**	**X**
CSA participation (outside of/in addition to the research study; household)	**X**	**X**	**X**
	Year 2	Year 3	Year 4
Process evaluation			
Program evaluation			
Dose delivered	**X**	**X**	**X**
Dose received	**X**	**X**	
Fidelity	**X**	**X**	
Experiences	**X**	**X**	
Program cost	**X**		
Non-participation	**X**		

^a^Subset of participants

##### Physical measures

Anthropometric and dermal measures will be collected at baseline and in the fall of Years 2–4.

**Anthropometric measures.** Anthropometric measures will be taken without shoes and in light clothing according to standard procedures [81]. Weight will be measured to the nearest 0.2 lbs. using the Seca Clara 803 scale. Height will be measured to the nearest 0.125 in. with the Seca 213 portable stadiometer. Weight and height measurements will be collected in duplicate unless the two measurements are more than 0.4 lbs. or 0.125 in. apart. In that case, a third measurement will be taken.

**Dermal carotenoid measures.** Dermal carotenoid levels will be assessed as an objective measure of fruit and vegetable intake. Study staff will use the Pharmanex Biophotonic Scanner S3 (NuSkin, Provo, UT), which non-invasively measures the concentration of carotenoids in skin tissues using resonance Raman spectroscopy, to scan a specific point of the palm of one hand. Dermal carotenoids will be measured in duplicate, unless the two measurements are greater than 2000 units apart. In that case, a third measurement will be taken. The same hand will be used at each assessment.

##### Dietary recalls

The National Cancer Institute’s Automated Self-Administered 24-h Recall system (ASA24–2016™) will be used to collect sets of three dietary recalls for the focal child [73]. This tool is based on the US Department of Agriculture’s interviewer-administered Automated Multiple-Pass Method (AMPM) and collects data on foods, drinks, and dietary supplements consumed the previous day. For children aged 2–5 years, the adult caregiver will complete the recall for the child. For children aged 6 years and older, the child will be asked to help the caregiver complete the recall.

##### Online questionnaires

Study participants will complete online questionnaires at baseline, in fall of Years 2–4, and spring of Years 3–4.

**Brief dietary measures.** Dietary intake of fruits and vegetables will be measured using the National Cancer Institute’s All-Day Fruit and Vegetable Screener (FVS) [82]. The FVS is a validated, 19-item instrument, which asks about the frequency and quantity of consumption of fruit and vegetables during the past month. We will adapt the FVS to an online format and add visual aids to improve portion size estimation [83]. Intake of sugar sweetened beverages and processed foods will be collected using the second version of the beverage and snack questionnaire (BSQ2) [84, 85]. The BSQ2 asks about frequency of consumption of beverages, savory snacks, and sweets in the last 7 days. To simplify the tool and reduce duplication with the FVS, we will remove questions about consumption of vegetables, fruits, or 100% fruit juice and will not ask participants to specify if foods were consumed in school or out of school. We also will ask whether eating habits in the past month were typical, the proportion of meals prepared and/or eaten together, and who completed the FVS and BSQ2 for the child.

**Fruit and vegetable knowledge, attitudes, and beliefs.** Caregivers’ *knowledge* of recommended fruit and vegetable consumption will be assessed by two ordinal variables, one with response choices in cups and the other relative to plate images. Caregivers’ *attitudes* toward food preparation will be captured by the Negative Cooking Attitude scale which sums ordinal responses to four negative statements about cooking [86]. The Self-Efficacy for Eating/Cooking Fruits and Vegetables scale [86] will be streamlined to focus only on items relating to fruits and vegetables, and record ordinal responses to four items. General nutrition *beliefs* will be assessed using the General Nutrition Knowledge Belief Score which sums ordinal responses to 11 healthy eating statements [87]. These beliefs include items directly relevant to F3HK, including the importance to participants of eating diets that include plenty of fruits and vegetables, use salt or sodium only in moderation, are low in saturated fat, and use sugars only in moderation.

**Caregiver’s ability to select, store, and prepare CSA produce.** The Cooking Techniques and Meal Preparation Self-Efficacy scale [86] assesses participant confidence in knife skills, preparation techniques, and basic cooking skills. We will expand the scale to include additional items that align with the aims and activities of the CSA-tailored education. Items on washing, storing, freezing, and drying produce will be added, as well as the preparation of leafy greens and cooking with herbs, onions, and garlic, which will be emphasized in the curriculum.

**Caregiver’s ability to substitute fruit and vegetables for energy-dense foods.** Caregivers will be asked about the monthly frequency of preparing nine specific fruit or vegetable-based snacks for their children (apple wedges, melon slices, plain berries, other fruits, carrot sticks, celery sticks, cucumber sticks, pepper slices, or other vegetables). The curriculum will emphasize substituting these particular foods for more energy-dense snacks.

**Caregiver’s ability to prepare foods to minimize added (solid) fat and sugar.** Caregivers will be asked about the monthly frequency of preparing for dinner those vegetables which are typically abundant in CSA shares (lettuce or other salad greens, green or red cabbage, other greens, potatoes, other root vegetables, and winter squash), and their most frequent preparation method for each (raw; steamed, boiled or baked; deep fat fried; roasted or sautéed in oil; cooked with meat, butter or cheese; or cooked another way).

**Fruit and vegetable availability and accessibility within the home.** Home fruit and vegetable availability will be assessed using questions from a 3-item scale, which asks caregivers “How often are the following true? 1) We have fruits and vegetables in my home, 2) In my home, vegetables are served at meals, 3) In my home, fruit is served for dessert” [88]. Home fruit and vegetable accessibility will be assessed using questions from a 4-item scale, which asks caregivers, “How often are the following true? 1) In my home, there is fruit available to have as a snack, 2) In my home, there is vegetable available to have as a snack, 3) In my home, there are cut-up vegetables in the fridge for my child to eat, and 4) In my home, there is fresh fruit on the counter, table, or somewhere else where my child can easily get to it” [88]. For both scales, four ordinal response options will be offered (hardly ever, rarely, sometimes, often). Caregivers also will be asked to report how easy or difficult it is to financially afford and physically access acceptable quality fruits and vegetables from five ordinal response options.

**Household food security.** Household food security will be classified by the 6-item short form of the USDA Food Security Survey Module (FSSM), with a 30-day reference period [89]. Items ask respondents about the conditions and experiences of food insufficiency due to resource limitations, and the behavioral responses of household members to these conditions. The form will be converted to an online format, but questions and response options will not be modified. Participants that affirm two or more items are considered to live in a food insecure household.

**Nutrition assistance and education participation.** Participation in school meal programs will be measured using seven questions from the National Health and Nutrition Examination Survey (NHANES) Diet Behavior and Nutrition Questionnaire [90]. Minor modifications will be made to simplify some questions and response options, and improve their suitability to an online format. We also will ask a follow-up question to determine whether the focal child’s school offers universal free breakfast. Three questions from the NHANES Food Security Module [91] will be used to assess participation in SNAP and the Special Supplemental Food Program for Women, Infants, and Children (WIC). These questions will be modified to specify a one-month reference period, rather than a one-year reference period. Study participants also will be asked if they participated in nutrition education classes other than those for the study since the last assessment, and, if yes, how many classes they attended.

**Physical activity and sedentary behavior.** To assess child physical activity, caregivers will be asked the number of days in past week the focal child was active for at least 60 min [92], and two questions about the amount of time the child “typically” spent playing outdoors in the last month – one related to weekdays and the other related to weekend days [93]. To assess sedentary behavior, caregivers will be asked to report the number of hours on an average school day that the focal child watches television, plays video games or computer games, or uses a computer for something that is not school work [92]. Questions drawn from the Middle School Youth Risk Behavior Survey [92] will be adapted for caregiver-report and to an online format.

**General health status.** Caregivers will be asked to report their general health and the general health of the focal child from five ordinal response options using questions from the NHANES converted to an online format [94]. They also will be asked to report how much time they (the adult) have spent outside per day between 10 am and 4 pm.

**Costs associated with food purchasing and preparation.** Caregivers will be asked 12 questions to assess (1) cooking supply costs; (2) grocery shopping expenses; (3) time and travel costs associated with shopping at the grocery store; (4) time spent planning meals; (5) time spent cooking meals; and (6) any costs associated with “eating out” or purchasing prepared meals and snacks not included in the reported grocery costs.

**Costs associated with CO-CSA participation (specified assessments only).** Costs associated with CO-CSA participation, including the time and financial costs associated with program participation and related food preparation behaviors, will be assessed in the fall each year the household is assigned to receive the CO-CSA. Questions will cover (1) employment and wages; (2) costs associated with travel to and from the CSA pick-up site and the F3HK healthy eating classes, including childcare costs, if applicable; (3) time spent at the pick-up site and healthy eating classes; and (4) the value of contributions to program success (e.g. volunteered time or donated supplies). Questions pertaining to the healthy eating classes will be asked only in the years and to the groups that the classes are offered.

**Kitchen inventory (baseline only).** At baseline, caregivers will be asked about ownership of 14 common kitchen implements (paring knife, chef’s knife, cutting board, spatula, cooking spoons, vegetable peeler, salad spinner, mixing bowl, frying/sauté pan, storage container, saucepan, colander, slow cooker, and food processor), how commonly they are used to prepare, cook, and store fresh fruit and vegetables, and their quality. For those that they do not own, caregivers will be asked which would make preparing, cooking, and storing fresh fruit and vegetables easier.

**Household composition and demographics.** At baseline, all adult participants will compete questions drawn from the American Community Survey [95] and BRFSS [96] about household composition (age, gender, and relationship of all household members) and demographic characteristics (race/ethnicity, education, employment, and household income). Questions and response options will be modified to an online format and simplified, where needed. Adult participants also will report whether anyone in the household smokes. Caregivers will be asked to provide the name, age, and gender of the focal child and the number of days in a typical week that he or she lives with the respondent.

On follow-up questionnaires, participants will be asked to update household composition, education, employment, income, smoking status, and days that child lives with respondent.

**CSA participation (outside of/in addition to the research study).** At each follow-up online survey, study participants will be asked if they participated in a CSA (not part of the intervention) during the CSA season since the last assessment.

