### Component 3: Develop skill-based, CSA-tailored education curriculum

The development of a CSA-tailored, skill-based nutrition education curriculum will be informed by components 1 (formative research) and 2 (longitudinal analysis). A curriculum advisory committee composed of extension education representatives from each of the four states will provide input and feedback throughout the curriculum development process. Information from existing EFNEP and Supplemental Nutrition Assistance Program Education (SNAP-Ed) curricula will be adapted and integrated, as appropriate.

Social Cognitive Theory [74], the Dietary Guidelines for Americans [75], and the Physical Activity Guidelines for Americans [76] will guide the design of learning objectives, education strategies and activities. The overarching objectives of the education will be to: (1) address attitudes and beliefs about the value of consuming fruits and vegetables (outcome expectation); (2) improve skills and self-efficacy with respect to storing, preparing, and consuming CSA produce (self-efficacy); (3) reduce potential barriers to acceptance of CSA produce and develop strategies to substitute fruits and vegetables for more energy-dense foods (barriers); (4) increase skills and self-efficacy related to preparation of CSA produce using minimal solid fat and sugar (behavioral capacity); (5) provide opportunities for participants to observe peers demonstrating newly acquired skills and share new experiences via group discussion (observational learning/modeling); and (6) provide information and strategies to help families be more active in daily life and reduce sedentary time, particularly screen time.

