##### Screening and eligibility

Potential participants will be screened for eligibility using an electronic tablet-based screening tool. The eligibility criteria for participation is: (1) age 18 years or older; (2) English-speaking; (3) parent or legal guardian of at least one child between 2 and 12 years of age in the household (herein referred to as a caregiver); (4) meet income requirements of ≤185% of FPL (self-reported); (5) have not participated in a CSA in the past 3 years; (6) be willing to use their SNAP benefits or their own money to purchase the 50% CO-CSA share; (7) have an active email address and access to a computer or tablet for online data collection; and (8) be willing to attend CSA-tailored education classes as part of the intervention.

To enroll into the study, participants must: (1) attend a baseline assessment visit and provide written consent; (2) complete the first online questionnaire; and (3) if assigned to intervention, pay the farm a deposit equal to two weekly CO-CSA payments (refundable at the end of the season if all payments are made). The decision to require a deposit draws on the experiences of a program that provided no-cost CSA shares to low-income consumers in North Carolina, which indicate participants may be more engaged with a CSA arrangement if they make a financial commitment [55].

In each participating household, one caregiver and one child aged 2–12 years (herein referred to as the focal child) will enroll in the study. Caregivers will provide written informed consent to take part and written permission for the focal child to participate. Children 7–12 years will provide oral assent. Consent and assent will be obtained by trained study staff. Any ancillary studies that develop out of this project will obtain participant consent separately. Informed consent materials are available as Additional file 1.

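### Child screen time is asked only for a school day, although focal children enroll from age 2 and need not attend school

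*Protocol article*

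**What the plan says.** Under Screening and eligibility, the caregiver must be a "parent or legal guardian of at least one child between 2 and 12 years of age in the household", and in each household "one caregiver and one child aged 2–12 years (herein referred to as the focal child) will enroll in the study". No criterion concerns school attendance.

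Table 4 lists child sedentary behavior among the secondary outcomes, with a youth risk behavior questionnaire as its only source, flagged as modified. The paragraph on physical activity and sedentary behavior (Online questionnaires) describes the measure. Caregivers give "the number of hours on an average school day that the focal child watches television"; gaming and computer use unrelated to school are counted with it, for the same reference day. On adaptation it says: "Questions drawn from the Middle School Youth Risk Behavior Survey [92] will be adapted for caregiver-report and to an online format". In the same paragraph the outdoor-play questions are asked twice, "one related to weekdays and the other related to weekend days".

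Table 5 schedules the child activity and sedentary module at baseline, fall and spring, with no age restriction. Component 3 makes it a curriculum objective to give information and strategies that "help families be more active in daily life and reduce sedentary time, particularly screen time". The section on analysis of intervention outcomes forms change scores by subtracting baseline from later values.

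**The concern.** The item comes from a middle-school survey, where every respondent has a school day. This trial includes children who may have none. A caregiver of a 2-year-old at home has no day to report on, and the article does not say what that caregiver should do. Plausible responses are to skip the item, or to answer for a childcare day or for any weekday. The article gives no basis for knowing which.

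Two further consequences follow. First, a child who is out of school at baseline and in school by the fall assessment contributes a change score whose two halves refer to different kinds of day, so school entry is mixed with any change in behavior. Second, the item is silent on weekends and holidays for children of every age. A family that cut screen time on those days, in line with the curriculum, would show no change on this outcome.

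**Working it through.** The article states no figure on this point, so there is none to reproduce. The check compares the text of several sections, then uses simple proportions for scale.

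**Text check**

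1. *Population.* Children aged 2 to 12, with no school criterion (Screening and eligibility).
2. *Item.* One reference day, the school day (Online questionnaires).
3. *Who is asked.* Every child at every questionnaire. Table 5 does mark a subset of participants for another item, the costs of CO-CSA participation, but none for this one.
4. *Adaptation.* Reporter and mode are named; day type and age are not. Elsewhere the article does report changes of this kind. The federal food-assistance questions are moved to a one-month reference period, the in-school/out-of-school distinction is dropped from the beverage and snack questionnaire, and the dietary recall procedure differs for ages 2–5 and for age 6 and over. The natural reading is that the school-day wording is kept.
5. *Weekend coverage.* Present for outdoor play and absent for screen time, within one paragraph.

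**Scale at baseline**

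Inputs: 240 households, one focal child each (Sample size calculations; Screening and eligibility). The age distribution is not given; I assume it is uniform over the 11 single-year ages 2 to 12.

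- Ages 2–4 without a school day: 3/11 = 27.3%; 0.273 × 240 ≈ 65 children.
- Ages 2–5 without a school day: 4/11 = 36.4%; 0.364 × 240 ≈ 87 children.

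The first is the more reasonable upper figure, because many 5-year-olds may be in school. Either falls if preschool counts as school, and rises if recruitment skews young.

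**Children who change reference day**

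The analysis section keeps Groups 1 and 2 in their randomized arms for Year 2 baseline, Year 2 fall and Year 3 spring, and Groups 3 and 4 for Year 3 spring, Year 3 fall and Year 4 spring. Each window contains about one school start. Under the same uniform-age assumption, that is about one single-year age group: 1/11 = 9.1%; 240/11 ≈ 22 children.

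**Days not covered**

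Weekends are 2/7 = 28.6% of days, a minimum because school holidays are also left out. If a family cuts screen time by *d* hours on each weekend day only, the school-day item changes by 0, whereas the weekly average changes by 2*d*/7. For *d* = 1 hour that is 0.29 hours per day.

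**The case against.** The strongest reply is that the article paraphrases an instrument it does not reproduce. Table 4 flags the tool as modified, and instruments are available on request. A skip rule or an alternative wording for preschool children could sit there, and the two adaptations named need not be all of them. This stands as a limit on certainty. It does not remove the point, because the article fixes the reference day in words and gives no exception.

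A second reply is that a school-day measure, though incomplete, can be compared between arms, and that the outdoor-play items differ because they come from another source. That is fair for children in school. It does not help children without a school day, and the difference in source explains the inconsistency without justifying it.

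A third reply is that the consequence is small: one of many secondary outcomes in a trial that describes itself as exploratory, with dietary primary outcomes and a sample size that does not depend on it. This also stands.

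A reader might infer more than the text supports:

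- *Bias between arms.* Families are randomized 1:1 within communities, so age and school entry are balanced in expectation. The fault adds noise and missing data and does not favor an arm.
- *School entry distorting three years of change scores.* Randomized assignment is kept for only about one school start; later measurements are not a randomized comparison.
- *Imputation of values that do not exist.* The article plans multiple imputation for partly missing data but does not say that not-applicable answers would be imputed.
- *Weekends as the days when families can most influence screen time.* Nothing in the article supports this. The point about weekends is coverage only.

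**Conclusion.** The point holds as a weakness in the measurement of a secondary outcome. As described, the sedentary-behavior item has no defined reference day for children not in school, can change its meaning for a child who starts school between baseline and fall, and omits non-school days for every child, although screen time is a target of the curriculum. The expected cost is missing or inconsistent answers, lower precision and incomplete coverage. The primary outcomes, the sample size and the randomization are unaffected.

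Up to about 27% of children (about 65 of 240) could lack an applicable baseline value, and about 9% (about 22) could change reference day within a randomized comparison. Both figures assume uniform ages from 2 to 12. The first also assumes that no child aged 2–4 attends anything a caregiver would call school, so it should be read as an upper figure under that assumption and not as a count of invalid answers. The omission of at least 2 in 7 days depends on no assumption about age.

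**What to change.** Word the item for *an average weekday*, whether or not the child attends school, and add the same item for *an average weekend day*, matching the outdoor-play questions. Define the sedentary outcome at every age and every assessment as

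(5 × weekday hours + 2 × weekend-day hours)/7.

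The cost is rewording questions that are already being adapted, plus one or two extra online items. The small downside is less direct comparison with published school-day survey figures. If the school-day wording is kept, the plan should at least state the ages to which the outcome applies and how the item is handled for children not in school; that would still leave weekends unmeasured.
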